### Secondary outcome measures

Secondary outcome measures include greater self-knowledge, the perception of emotional triggers for overeating, increase in self-compassion resulting in higher self-care and better adherence to treatment, improvement of nutritional status (reduction of body weight by ≥ 5%) and biochemical examinations throughout the intervention, as well as maintenance of this status (without weight regain) during a 3-month follow-up period. This maintenance could lead to the prevention of multiple morbidities related to excess body weight. Levels of mindfulness, stress, anxiety (psychometric scale and serum cortisol) and self-compassion will be assessed. Body composition, basal metabolism and food intake, as well as maintenance of practices and the feasibility of the programme, will be also evaluated. Changes in lifestyles and eating patterns of participants in each group will be evaluated at the end of the programme and 3 months after the intervention.

### Data handling

All study-related information will be stored in secure folders with limited access. Paper-based data collection forms will contain only participant numbers to maintain confidentiality and will be stored in a locked cabinet in an area with limited access. Electronic data files will be password-protected (RedCap). The list linking participant numbers and personal information will be stored in a separate password-protected file. Paper-based data entry will be double-checked. Data will be stored for 5 years after the end of inclusion. The study has low negligibility risks; therefore, no data monitoring committee will be assigned. Only the first author and lead researchers, or persons assigned by them, will have access to the final dataset. Authors of the final trial report will make substantial contributions to the design, conduct, interpretation and reporting of the trial. Study results will be presented via publications and presentations; study participants, funders and involved clinicians will receive a summary of the study results.

### Data analysis

The qualitative variables will be described as numbers and percentages, and quantitative data will be summarised as mean values with SD if the assumption of normality of data has been satisfied; otherwise, the median and 25% and 75% percentiles will be used. The three conditions for the treatment will be compared with baseline measures to evaluate the success of randomisation. In this case, the chi-square test or Fisher’s exact test for qualitative variables will be used, and one-way ANOVA or the Kruskal-Wallis test will be applied for quantitative variables.

Longitudinal data (T0, T1 and T2) will be collected for each group, which means that they will not be independent; therefore, repeated-measures ANOVA will be used. When assessing the effectiveness of the TAU programme, repeated-measures ANOVA will be used to assess the main effects of time and treatment, and the interaction between them. The analysis will be performed with the complete sample, and we plan to perform analyses in subgroups stratified by BMI. The models will be adjusted for possible confounding variables, such as age, BMI and other relevant covariates. Differences will be identified by using test linear hypotheses after ANOVA, and multiple testing will be adjusted by the Bonferroni correction.

The data will be evaluated for the intention-to-treat analysis; that is, the analysis will include all participants after randomisation. For the per-protocol analysis, women in the intervention groups who do not participate in at least four sessions will be excluded. For the attrition analysis, we will compare women who complete the protocol with women who answered only the baseline questionnaire.

All data analysis will be performed with STATA version 14.2 software (StataCorp, College Station, TX, USA) [58]. *p* Values < 0.05 will be considered statistically significant. No datasets were generated or analysed during the present study.

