### Measures

#### Socio-demographic health and quality of life

Data to be collected include age, sex, marital status, education level, professional status, number of hours of sleep, morbidity profile and bowel habits.

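### Significance tests of baseline measures cannot show whether randomisation succeeded, and by chance alone would probably give at least one p < 0.05

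*Protocol article*

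**What the plan says.** All the relevant text on the tests is in the Data analysis section of the protocol article.

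- Purpose: the arms are set against each other at baseline, and the reason given is "to evaluate the success of randomisation".
- Method for categorical data: "the chi-square test or Fisher’s exact test for qualitative variables will be used".
- Method for continuous data: "one-way ANOVA or the Kruskal-Wallis test will be applied for quantitative variables".
- Threshold, stated once for the whole section: "Values < 0.05 will be considered statistically significant".
- Multiplicity, in the paragraph on the longitudinal outcome models: "Differences will be identified by using test linear hypotheses after ANOVA, and multiple testing will be adjusted by the Bonferroni correction". Nothing extends this correction to the baseline tests.
- Adjustment, also in the outcome paragraph: "The models will be adjusted for possible confounding variables, such as age, BMI and other relevant covariates".

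The Recruitment section describes software-generated permuted blocks with equal allocation to three arms. The opening of Methods/design says that allocation is stratified by weight status. T0 instruments are applied before randomisation, and participants do not learn their arm until the first meeting.

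**The concern.** The purpose, the tests and the threshold are all written down, so this is not a detail left to an analysis plan. The difficulty is logical. A significance test asks whether chance can explain a difference between arms. Under properly executed random allocation, chance is the only explanation for a difference in something measured before allocation. The test therefore asks a question whose answer is already known, and its result in either direction does not grade the randomisation.

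Two things are at stake. First, with many baseline variables, one or more small p-values are likely even when nothing has gone wrong, and the stated purpose invites the report to present them as a defect in randomisation. Second, a baseline p-value carries no information on whether a variable predicts the outcome, so it is a poor guide to covariate choice if anyone uses it that way. The open end of the adjustment sentence leaves room for that use without prescribing it.

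**Working it through.** The protocol states neither a number of baseline tests nor a false-positive rate, so there is no figure of its own to reproduce.

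**Inputs**

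- Level per test: 0.05 (Data analysis).
- Socio-demographic items: "age, sex, marital status, education level, professional status, number of hours of sleep, morbidity profile and bowel habits". That is 8 items. Sex is constant in an all-female trial, which leaves 7.
- Table 1: 20 rows are marked at baseline.
- Central count, an assumption: K = 20 + 7 = 27, at one test per row. Splitting the DEBQ, HADS, lipid, anthropometry and body-composition rows would raise it. The range considered is 20 to 40.
- Arms: 3 of 80 (Participants and setting).

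**Independent tests, all nulls true**

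P(at least one p < 0.05) = 1 − 0.95^K, and the expected number of such results is 0.05 × K.

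| K | P(at least one) | Expected number |
|---|---|---|
| 10 | 40.1% | 0.50 |
| 13 | 48.7% | 0.65 |
| 14 | 51.2% | 0.70 |
| 20 | 64.2% | 1.00 |
| 27 | 75.0% | 1.35 |
| 40 | 87.2% | 2.00 |

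For K = 27: 1 − 0.95^27 = 0.750. The probability passes one half at K = 14.

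**Correlated variables**

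Many Table 1 measures overlap: the eating scales, the weight and body-composition measures, and the glycaemic measures. This was checked by simulation with 3 arms of 80, K normal variables, one-way ANOVA at 0.05 and 4,000 runs per setting. The Monte Carlo standard error is at most √(0.25/4000) = 0.008. Correlation was imposed either within blocks of five variables or between all pairs.

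| Structure | Correlation | K = 20 | K = 27 |
|---|---|---|---|
| Blocks of 5 | 0.3 | 61% | 72% |
| Blocks of 5 | 0.5 | 57% | 68% |
| Blocks of 5 | 0.7 | 49% | 59% |
| All pairs | 0.2 | 59% | 69% |
| All pairs | 0.3 | 52% | 62% |
| All pairs | 0.5 | 43% | 50% |
| All pairs | 0.7 | 30% | 34% |

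The block structure is the more plausible one, since a lipid fraction and an education level have little reason to be strongly correlated. The documents give no correlations, so this is a judgement.

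**If Bonferroni were applied to the baseline tests**

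1 − (1 − 0.05/K)^K is about 4.9% for any K from 20 to 40. The false signals would become rare, but the tests would still not answer the question put to them.

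**The case against.** The strongest objection is that a reader might infer two things that the documents do not say.

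- *That any single p < 0.05 counts as failed randomisation.* The Data analysis section gives a purpose and a general threshold, but no decision rule and no consequence. The percentages above are therefore the chance that at least one baseline result reaches p < 0.05, and not the chance that the trial declares failure.
- *That the baseline tests select the adjustment covariates.* The two sentences stand in different paragraphs and nothing joins them. Age and BMI are named whatever the baseline table shows. The unnamed remainder may be listed in an analysis plan that is not shown, so the open list is no finding by itself. It follows that a distorted error rate in the primary analysis is not established.

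Both objections stand and limit the point.

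Three further objections stand in part. First, the 75% figure needs independence and a count that the protocol does not give. With strong correlation across all variables it falls to a half or lower. Second, stratification by weight status makes tests on weight-related variables reject less often than 5%, which lowers the figures somewhat. Third, the article does not describe concealment from recruiting staff, so the statement that the null is true depends on allocation being run as described. One could argue that baseline tests would help to detect a breach. They would do so poorly, because a signal that appears in most sound trials cannot separate a sound one from a compromised one.

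The T0 outcome is also not ignored at present, because it enters the repeated-measures ANOVA as one of the three responses. That affects how the remedy must be worded.

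**Conclusion.** The point holds in a limited form. The plan assigns to baseline significance tests a task that they cannot perform, and this follows from the allocation method that the plan itself describes. With 27 variables, chance alone gives at least one p < 0.05 in about 75% of trials if the variables are independent, about 59% to 72% with block correlation of 0.7 down to 0.3, and about 50% or less if every pair is correlated at 0.5 or more. These figures assume one test per listed variable, no multiplicity correction at baseline, and allocation carried out as described.

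The documents do not show that a significant baseline result would trigger any action or decide the adjusted model. The defect is minor: it does not invalidate the trial, but it can lead to a misleading statement about randomisation in the report.

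**What to change.** 1. Delete the baseline significance tests and the words "to evaluate the success of randomisation". Keep the descriptive summaries that the section already plans, given by arm and without p-values. Whether randomisation was sound is better shown by reporting how the sequence was generated, concealed and followed.
2. State that adjustment covariates are fixed independently of the baseline table: the randomisation stratum (weight status), age, and the T0 value of the outcome.
3. If T0 is a covariate, make T1 and T2 the only responses in the longitudinal model, so that T0 is not used twice. This departs from the present repeated-measures ANOVA on T0, T1 and T2 and should be written out explicitly.

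The first step only removes tests. The second and third are a small change of model specification. All the variables are already collected, so data collection does not change.

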### Participants and setting

The sample will comprise 240 female adults with excess weight (overweight or obese) who attend PC spontaneously and of their own accord, especially in the Santo Amaro (São Paulo), and who meet the inclusion criteria for the study. Power analysis was calculated a priori using G*Power 3.1 [22] for repeated-measures analysis of variance (ANOVA). The results indicated that a sample size of 240 (*n* = 80 per group) is needed, with a significance level of 5% and a power of 80% to detect significant main effects of group and time, with a small to moderate effect size (Cohen’s *f* = 0.25), and allowing for a dropout rate of about 20%.

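### The intention-to-treat promise and the power statement do not fit the repeated-measures ANOVA: name a baseline-adjusted arm contrast on all available data as primary

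*Protocol article*

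**What the plan says.** All places are in the protocol article.

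- **Data analysis, method.** Over T0, T1 and T2, "repeated-measures ANOVA will be used to assess the main effects of time and treatment, and the interaction between them". Linear hypotheses are then tested with a Bonferroni correction. The sentence names TAU as the programme being assessed.
- **Data analysis, analysis set.** The analysis is by intention to treat: "the analysis will include all participants after randomisation". The same section plans an attrition comparison with women who gave only baseline questionnaires, so it expects such women.
- **Participants and setting.** The sample of 240 (80 per group) is set "to detect significant main effects of group and time", at 5% significance, 80% power and Cohen's f of 0.25, "allowing for a dropout rate of about 20" per cent. The interaction is not mentioned there.
- **Recruitment.** A woman who attends fewer than half plus one of the programme sessions counts as a dropout.
- **Follow-up assessments.** Questionnaires are given before each group's first and last sessions and again at follow-up.

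**The concern.** There are two mismatches.

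**Analysis set against method.** Whether the named method can carry the promised set depends on how it is run. In its classical form it needs all three visits, so the result would be a completer analysis under an intention-to-treat label. The loss is also unlikely to be neutral between arms. In MBHP and MB-EAT, dropout is defined by session attendance and the T1 questionnaires are tied to the last session. TAU has no programme sessions. A completer comparison would therefore set attenders of the two programmes against TAU women who were not selected in that way.

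**Power target against treatment effect.** The trial is sized on two terms that do not measure the treatment effect. The group main effect mixes in the baseline visit, where randomisation makes the expected difference zero. The time main effect would be significant if all three arms, TAU included, improved equally. The term that does measure it is in the model, but nothing gives it priority.

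**Working it through.** **Inputs from the protocol article:** 240 women, 80 per group, 1:1:1; 5% significance; 80% power; f = 0.25, equivalent to d = 0.5 for two groups; about 20% dropout; visits T0, T1 and T2.

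**Assumptions, not in the document:** compound symmetry; correlation ρ between visits of 0.3, 0.5 or 0.7; effect d = 0.5 SD at both T1 and T2; equal baselines; two-sided 5% pairwise tests without Bonferroni; normal approximation.

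**1. The plan's own figure.** A comparison of two means with d = 0.5 needs 2(1.960 + 0.842)²/0.5² = 62.8, so 63 per arm. Then 63/0.8 = 78.75, so 79 per arm and 237 in all. With 64 per arm, 64/0.8 = 80 exactly, which is 240. A group-by-time F test with 4 numerator degrees of freedom and noncentrality f²N needs 195, or 244 after dropout.

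The group main effect that the text names has noncentrality f²N·3/(1+2ρ). It needs 57, 108 and 159 women at ρ = 0, 0.5 and 1, or 72, 135 and 199 after dropout. So 240 is reached by other routes but is not too small for its stated target.

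**2. Women affected.** 0.20 × 240 = 48, which leaves 192, or 64 per arm.

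**3. What the group main effect estimates.** With differences 0, d and d at T0, T1 and T2, the average is (0 + d + d)/3 = 2d/3. For d = 0.5 this is 0.333 SD. This holds at any correlation. Conversely, a main effect of 0.5 SD needs a post-baseline effect of 0.5/(2/3) = 0.75 SD. That is why step 1 looks comfortable and step 4 does not.

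**4. Power with 64 per arm.** The standard error of an arm difference is √(2v/64), where v is:
- group main effect: (1+2ρ)/3
- mean of T1 and T2 minus T0 (interaction contrast): (1+ρ)/2 + 1 − 2ρ = 1.5(1−ρ)
- baseline-adjusted mean of T1 and T2: (1+ρ)/2 − ρ²

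At ρ = 0.5:
- main effect: v = 0.667, SE = 0.144, 0.333/0.144 = 2.31, power Φ(2.31 − 1.96) = 64%
- interaction contrast: v = 0.75, SE = 0.153, 0.5/0.153 = 3.27, power 90%
- adjusted mean: v = 0.50, SE = 0.125, 0.5/0.125 = 4.00, power 98%

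| Contrast | Estimates | ρ = 0.3 | ρ = 0.5 | ρ = 0.7 |
|---|---|---|---|---|
| Group main effect | 0.333 SD | 73% | 64% | 56% |
| Post minus baseline interaction | 0.5 SD | 79% | 90% | 99% |
| Baseline-adjusted mean of T1 and T2 | 0.5 SD | 97% | 98% | 99.7% |

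Bonferroni correction lowers every entry.

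**5. Possible bias from dropout.** This is an illustrative simulation with no true effect and 20% dropout before T2 in each arm, linked to a poor T1 score in one arm only. Visit correlations were 0.5 (T0–T1), 0.4 (T0–T2) and 0.7 (T1–T2).
- Listwise ANOVA: false effects of −0.10 SD (T1−T0), −0.04 SD (T2−T0) and −0.14 SD (group main effect).
- Long-form ANOVA on available rows: 0.00 and 0.02 SD for the T1 and T2 interaction terms.
- Likelihood-type estimate under missing at random: 0.00 SD at T2.

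The simulation has no baseline-only women. In a long-form fit with subject effects, such women contribute nothing to change from baseline.

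**The case against.** **The method does not rule out intention to treat.** A reader might infer that repeated-measures ANOVA cannot deliver the promised set. The article does not support that. It never says listwise deletion. Stata, the named software, fits long-form ANOVA to unbalanced data, and imputation could be combined with ANOVA. The simulated long-form bias was near zero. An article may also leave missing-data detail to a fuller document. This stands, and it limits the point: the promise holds in one form of the method and fails in another, and the long form still relies on compound symmetry. The attendance rule likewise does not say that data from low attenders are discarded.

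**The treatment contrast is already in the plan.** The interaction and the later linear hypotheses are listed, so it would be wrong to say that the plan tests only main effects or will claim benefit from a time effect. This stands too. What remains is that no term is named as primary and the power statement covers only the other two.

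**The efficiency loss can be overstated.** At ρ = 0.5 the group main effect has one third of the efficiency of the adjusted mean (variance-scaled, (0.816/1.414)² = 0.33). A reader might take that as the plan's loss. It leaves out the interaction contrast, which reaches roughly the planned 80% or more across the range.

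**Dropout is already in the sample size.** Losing 48 women is therefore not an unplanned loss of precision; the issue is bias. Nor does step 1 suggest that 240 is too few for the stated target.

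**Conclusion.** The concern holds in a limited form.

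- The promise to analyse all randomised women is not secured by the named method when about 48 of 240 are expected to drop out and loss in the active arms is tied to attendance.
- The power statement targets a group main effect that recovers two thirds of a constant post-baseline effect, and a time main effect that is not a comparison of arms. The relevant interaction is present but without priority.

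The two-thirds dilution follows from the design if the effect is constant after baseline. The power figures rest on the assumed correlations, compound symmetry, d = 0.5 and the absence of Bonferroni correction. The bias sizes rest on an assumed dropout mechanism and show direction only.

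The change is worth making even against the plan's best term. At ρ = 0.5 the baseline-adjusted mean has v = 0.50 against 0.75 for the interaction contrast, a one-third smaller variance. Naming TAU as the programme assessed is a wording slip, since the aims and hypotheses make the comparison clear.

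**What to change.** 1. Make the primary analysis a linear mixed model on all available data from all randomised women, with the T0 mean constrained equal across arms or baseline adjusted for. An unstructured covariance removes the reliance on compound symmetry. The model is valid under missing at random, which should be stated.
2. Take the arm contrasts at T1 and T2 as the treatment effects: MBHP+TAU against TAU, MB-EAT+TAU against TAU, and MB-EAT against MBHP. State that neither the time nor the group main effect counts as evidence of efficacy.
3. Restate the power in Participants and setting for the chosen contrast, giving the assumed correlation and the Bonferroni correction.
4. Add one missing-not-at-random sensitivity analysis, for example shifting the imputed values of dropouts in the active arms.
5. Correct the sentence that names TAU as the programme assessed.

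Naming the group-by-time contrast as primary, with a stated missing-data method, would also resolve the mismatch, with less precision. The cost is wording, one Stata mixed-model command, a little more analysis work and a restated power figure. No new data are needed. The Trial status section says recruitment was still under way at submission, so the change could be made before analysis.

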### Follow-up assessments

The evaluations for the main outcome (eating behaviour) and the secondary outcomes (mindfulness skills, self-compassion, nutritional status, depression and stress) will occur at baseline (T0), immediately after the 8- or 10-week intervention (T1) and at 3 months post-intervention (T2) (*see* Table 1). The outcomes of the practices, unexpected (adverse) effects and maintenance of and adherence to practices will all be evaluated in the T1–T2 intervals. The estimated time for completing the questionnaires and other evaluations is approximately 90 minutes, and the questionnaires will be administered before the beginning of the first and last sessions of each group, as well as at follow-up. For groups G2 and G3, one session will be offered each month to cultivate and strengthen the practice of mindfulness in the group, according to the practices described in each protocol. After the 3-month follow-up, the control group will be offered what is determined to be the most effective intervention, either MB-EAT or MBHP (Table 1).

**Table 1 Tab1:** Overview of measures and corresponding measurement time points

Measure	Target concept	Baseline	T1	T2
BES	Binge eating	x	x	x
BPAAT	Physical activity	x	x	x
DEBQ	Food style	x	x	x
EAT-26	Presence of abnormal eating patterns	x	x	x
HADS	Anxiety and depression symptoms	x	x	x
MAAS	Mindfulness skills	x	x	x
FFQ	Food Frequency Questionnaire	x	x	x
SCS	Self-compassion	x	x	x
Transtheoretical Model	Behaviour change	x	x	x
Feasibility Questionnaire	Feasibility of intervention		x	
Adverse effects questionnaire	Occurrence adverse effects		x	x
Amount of weekly practices	Adherence to practice		x	x
Anthropometry	Change in weight	x	x	x
Basal metabolic rate	Basal metabolism	x	x	x
Body composition	Fat mass and lean mass	x	x	x
BDNF	Brain-derived neurotrophic factor	x	x	x
Cortisol serum	Stress	x	x	x
Fasting blood glucose	Glycaemic control	x	x	x
HbA1c	Haemoglobin A1c	x	x	x
Insulin	Insulin	x	x	x
US-CRP	Ultra-sensitive C-reactive protein	x	x	x
Total cholesterol, fractions and TGL	Lipid profile	x	x	x
Alpha-1-glycoprotein	Inflammatory process	x	x	x
Focus group	Qualitative analysis		x	x

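### Arm-by-visit contrasts taken after a repeated-measures ANOVA share one pooled error term; unless sphericity holds, the T0-T2 contrast is mis-sized, and too liberal if correlation falls with time

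*Protocol article*

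**What the plan says.** The Data analysis section notes that each woman's T0, T1 and T2 values are correlated, so "they will not be independent; therefore, repeated-measures ANOVA will be used". The effects are named: "repeated-measures ANOVA will be used to assess the main effects of time and treatment, and the interaction between them". The step that compares the arms is also named: "Differences will be identified by using test linear hypotheses after ANOVA, and multiple testing will be adjusted by the Bonferroni correction". The threshold is "Values < 0.05 will be considered statistically significant".

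The Follow-up assessments section sets the visits at baseline (T0), "immediately after the 8- or 10-week intervention (T1) and at 3 months post-intervention (T2"). Table 1 shows DEBQ and BES, the primary instruments, at all three.

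The section does not list the contrasts or say how many there are. It names no error term for them, no covariance structure and no provision for non-sphericity. No between-visit correlation or standard deviation appears anywhere in the article.

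**The concern.** In a univariate repeated-measures ANOVA every within-woman comparison is judged against one residual mean square. That quantity averages over the three visit pairs. If the pairs differ in variability, the average is too small for the most variable pair and too large for the least variable one.

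The intervals here are 8-10 weeks (T0 to T1), 3 months (T1 to T2) and about 5 months (T0 to T2). Correlation commonly weakens as visits lie further apart, which would make the T0-T2 change the most variable and its standard error too small. Bonferroni does not cure this, because it rescales p values that are already wrong. An epsilon correction acts on the omnibus F test and leaves the contrasts as they were.

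At stake are the durable-effect comparisons at T2: each programme against TAU, and MB-EAT against MBHP. The article also says that after the 3-month follow-up the control group will be offered the programme found more effective, so a T2 comparison that rejects too readily could carry weight.

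**Working it through.** **Inputs from the article.** Three arms, 80 women per arm, about 20% dropout, so 80 × 0.80 = 64 per arm; three visits; nominal 5% (taken as two-sided).

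**Assumed, because the article is silent.** Equal standard deviations (set to 1), and correlations written as r01/r12/r02 for T0-T1, T1-T2 and T0-T2.

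**Formulas.**
- Variance of a difference between visits s and t: V_st = 2(1 − r_st).
- Pooled term, on the same scale: P = (V01 + V12 + V02)/3.
- Standard error used divided by the true one: k = √(P/V_st).
- Actual error rate at nominal 5%: 2[1 − Φ(1.96 k)].

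**The plan's nominal 5% first.** With equal correlations, V01 = V12 = V02, so k = 1 and the rate is 5.0%. The plan's figure is reproduced under sphericity.

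**One decaying pattern in full, 0.7/0.7/0.5.**
- V01 = 0.6, V12 = 0.6, V02 = 1.0; P = 2.2/3 = 0.733.
- T0-T2: k = √0.733 = 0.856, so the standard error is 14% too small; 1.96 × 0.856 = 1.678; rate 9.3%.
- T0-T1: k = √(0.733/0.6) = 1.106; 1.96 × 1.106 = 2.167; rate 3.0%.

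**Other patterns, same formulas.**

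| r01/r12/r02 | T0-T2 rate | T0-T1 rate |
|---|---|---|
| 0.2/0.2/0.04 | 6.5% | 4.3% |
| 0.6/0.6/0.5 | 6.8% | 4.1% |
| 0.5/0.7/0.5 | 6.8% | 6.8% |
| 0.6/0.8/0.55 | 8.4% | 6.7% |
| 0.8/0.8/0.64 | 10.0% | 2.7% |
| 0.5/0.7/0.6 | 5.0% | 8.0% |
| 0.5/0.5/0.55 | 4.2% | 5.4% |

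The last two rows show that the T0-T2 contrast is not inflated when T0-T2 is not the least correlated pair.

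**Simulation check** (3 arms × 64 women, 20,000 null trials per pattern). The pooled-term T0-T2 contrast rejected in 9.1% of trials for 0.7/0.7/0.5, 7.0% for 0.6/0.6/0.5 and 10.1% for 0.8/0.8/0.64. With the contrast's own error term, simulated rates stayed at 4.9-5.3% in every pattern tried.

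**Familywise error after Bonferroni, pattern 0.7/0.7/0.5, by simulation.**
- Three contrasts (three arm pairs, T0-T2): about 10%.
- Six contrasts (adding T0-T1): 6.8%.
- Nine contrasts (adding T1-T2): 5.5%.

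The larger families look better because the conservative short-interval contrasts use little of their share of alpha and the T0-T2 threshold becomes stricter.

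**The case against.** **The size is assumed.** A reader might infer that the plan's T2 comparison has a 7-10% error rate as a matter of fact. The article does not support that: it gives no correlations, and the rate is 5% under sphericity and can be lower. A further argument, that the programme falls between T0 and both later visits, does not single out T0-T2 either. Varied response to a programme lowers r01 and r02 together, which gives the milder 6.8% of the 0.5/0.7/0.5 pattern. This objection stands, and the figures are conditional.

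**The contrast is not named.** The article lists no T0-T2 contrast, and a fuller plan may specify the contrasts and their error term. The treatment main effect, tested against between-woman error, does not depend on sphericity. This stands as a limit on scope. It does not remove the point, because the article itself fixes the route: repeated-measures ANOVA, then linear hypotheses from it.

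**The family is not fixed.** The figure of about 10% applies only if Bonferroni covers three T2 contrasts. If contrasts are examined only after a significant interaction, the familywise error when no arm differs cannot exceed that of the omnibus test, which simulates at 5.2-6.2% uncorrected and 4.8-5.0% with an epsilon correction. This also stands, but the article states no such gate. A gate would also protect only when no arm differs. If both programmes beat TAU equally, it opens, and the MB-EAT versus MBHP contrast at T2 again relies on the pooled term. At 0.05/3 = 1.67% nominal, 0.7/0.7/0.5 gives 2[1 − Φ(2.394 × 0.856)] = 4.0%.

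**Not every T2 outcome is touched.** A reader might extend the point to all secondary outcomes. Weight reduction of at least 5% is binary, and adverse effects and amount of practice are recorded only at T1 and T2, so the sphericity argument does not reach them.

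**Conclusion.** The point holds in conditional form. The stated method gives every arm-by-visit contrast the same within-woman error term, which is valid only under sphericity, and nothing in the article supports sphericity for three unequally spaced visits. If correlation decays with time, the T0-T2 contrast is anticonservative by a modest amount, about 6.5-10% at nominal 5% across the assumed decaying patterns, and T0-T1 is often conservative. These figures rest on equal standard deviations, 64 completers per arm and assumed correlations.

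The scope is continuous outcomes measured at all three visits, DEBQ and BES among them. It is a choice that should be changed because the remedy is cheap and works whether or not sphericity holds. It is not evidence that the trial's conclusions will be wrong.

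**What to change.** Estimate the arm contrasts at T1 and T2 from a linear mixed model for repeated measures with an unstructured within-woman covariance over the three visits. Alternatively, test each arm difference in T0-T1 and T0-T2 change against the error term of that change. Apply the Bonferroni adjustment to the resulting p values, and state which contrasts form the family, since the familywise rate depends on it.

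The cost is one sentence in the plan and a model option in the named software. Error degrees of freedom fall from (192 − 3) × 2 = 378 to 192 − 3 = 189, which is negligible. When correlations decay, T2 intervals widen: for 0.7/0.7/0.5 by a factor of 1/0.856 = 1.17, which is the width they should have had. Little is lost if sphericity does hold.
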